#### Analysis of primary variable

AEs will be summarized for the safety population using the latest version of the MedDRA as well as the National Cancer Institute (NCI) Common Terminology Criteria for Adverse Events (CTCAE) v5.0. Incidence proportions will be calculated based on the total number of patients valid for safety and calculated by MedDRA System Organ Class, Preferred Term, and worst CTCAE grade. These analyses will be performed for TEAEs, drug-related TEAEs, treatment-emergent SAEs, drug-related treatment-emergent SAEs, and TEAEs leading to dose reduction, dose interruption, or permanent dose discontinuation. In addition, exposure-adjusted incidence rates will be summarized for TEAEs, defined as the total number of subjects with the AE divided by total subject time at risk in years.

For vital signs, descriptive statistics will be calculated by visit. Summary statistics on change from baseline for laboratory parameters will be reported for each visit. The change from baseline to worst post-baseline value will also be summarized. Where possible, laboratory data will be graded using the mapping provided within the NCI-CTCAE manual version that is valid at the time of analysis. CTCAE severity grading for laboratory abnormalities is mainly based on applicable laboratory threshold values outlined in NCI-CTCAE manuals. Frequency of laboratory abnormalities will be tabulated by NCI-CTCAE category and worst grade as well as by changes in severity from baseline to worst value post-baseline.

#### Analysis of secondary variables

All summaries with respect to effectiveness data will be descriptive. The primary data source for effectiveness endpoints ORR, disease control rate (DCR), DOR, time to response (TTR), and PFS will be based on tumor response as assessed by the investigator for the full analysis set. The estimates of ORR and DCR and the corresponding confidence intervals (CIs) will be provided. For the time-to-event variables DOR, PFS, and OS, the medians and survival rates at various time points with 95% CI will be estimated by the Kaplan–Meier method. TTR will be summarized for responders only using descriptive statistics. Radiologically or clinically documented progression of tumor will be considered as disease progression. Subgroup analyses stratified by prognostic, predictive, or other factors collected at baseline, as mentioned earlier, may be explored.

Duration of larotrectinib treatment is defined as the time (months) from the start of larotrectinib treatment to the day of permanent discontinuation (including death). For larotrectinib treatment, descriptive statistics will be calculated for the treatment duration, starting dose, and average dose. In addition, duration of larotrectinib treatment will be analyzed using a Kaplan–Meier approach, censoring subjects who have ongoing treatment at the time of analysis. The following data will be summarized for larotrectinib treatment: the number of patients with dose modification (e.g., reduction, interruption, re-challenge at protocol dose), number of dose modifications, and frequencies of reasons for dose modifications and permanent discontinuation.

For the pediatric cohort only, change in height and weight from baseline will be summarized at each visit. Age at adrenarche for males and menarche for females will be summarized. In addition, the number and percentage of patients with abnormal Tanner stage, abnormal neurological assessments, and abnormal developmental milestones will be presented.

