Results from these clinical trials demonstrated that in addition to having tumor-agnostic activity, larotrectinib is also effective across age groups, including in children and adolescents. Of the 159 patients analyzed in the integrated dataset, 52 (33%) were aged < 18 years old [29]. Tumor types included infantile fibrosarcoma (56%), other soft tissue sarcoma (37%), thyroid (4%), congenital mesoblastic nephroma (2%), and melanoma (2%). ORR was 92%; at the time of data analysis, medians for DOR, PFS, and OS were not reached. With the duration of treatment ranging from 1.3 + to 34.0 + months, larotrectinib was well tolerated with low rates of discontinuation due to treatment-related AEs and low rates of neurologic AEs.

Longer-term safety evaluation is required, and this is particularly relevant for pediatric patients in order to investigate potential developmental effects of treatment. There are limited available data on the safety profile of larotrectinib in a broader population and over a longer time period. Real-world safety and effectiveness data in a larger patient population are needed with a longer-term follow-up. The ON-TRK study is a prospective, open-label, multicenter, multi-cohort, non-interventional study in patients with locally advanced or metastatic TRK fusion cancer treated with larotrectinib. The aim of the ON-TRK study is to describe the safety and effectiveness of larotrectinib in this patient population under real-world conditions in standard clinical practice. As it is a post-approval safety study, it is also designed to fulfill FDA requirements for the accelerated approval of larotrectinib, which include additional studies to validate and describe the clinical benefits of larotrectinib. Post-approval commitments set forth in the FDA’s accelerated approval of larotrectinib require enough pediatric patients be followed for 5 years to evaluate the risk of potential long-term adverse effects of larotrectinib on growth and development and the assessment of unexpected risks of serious AEs (SAEs) in patients requiring a third larotrectinib dose modification due to toxicity [30]. This study is also intended to fulfill the post-marketing requirements set forth by the regulatory bodies of Canada and South Korea, and is part of the risk management plan provided to the EMA [31].

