**Fig. 1 Fig1:**
[figure not shown]
Study design. *NTRK* neurotrophic tyrosine receptor kinase, *TRK* tropomyosin receptor kinase

*NTRK* gene fusions will be detected locally by NGS, FISH, RT-PCR, or any other genomic test able to detect *NTRK* gene fusions. Cohorts will be defined by the tumor types of enrolled adult patients, including gastrointestinal, head and neck, lung, soft tissue sarcoma, primary CNS, melanoma, or ‘other’. All pediatric patients, regardless of tumor type, will be enrolled within a ‘pediatric’ cohort. Per the study protocol, central pathological review is not planned; all pathology data will be collated locally at each study site. The decision on the dose and duration of treatment is solely at the discretion of the treating physician, based on the recommendations included in the local product information. Examinations and the laboratory monitoring schedule will follow local label recommendations in line with local standard of care.

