### Objectives

The study objectives and associated variables are listed in Table 2. Up to 300 patients with *NTRK* gene fusion cancer will be included in this analysis. As the primary objective of this study is to describe the incidence of treatment-emergent AEs (TEAEs) in a real-world setting, the rationale for this study size was based on the probability of observing at least one TEAE event for a range of true incidence rates, including some of the uncommon events. For a true event incidence of 1% and a sample size of 300 patients, the probability of observing at least one event is 95%. Therefore, a total of approximately 300 patients was considered sufficient to observe at least one AE for even uncommon events.

**Table 2 Tab2:** Study objectives and variables

Objective	Variables
**Primary**: safety of larotrectinib in adult and pediatric patients with locally advanced or metastatic TRK fusion cancer	TEAEs in real-world practice conditions • Incidence • Severity • Seriousness • Outcome • Causality assessment (ARs)
**Secondary**: • Effectiveness of larotrectinib as per investigator assessment in the total study population as well as in patient subgroups (including, but not limited to, age, *NTRK* gene, *NTRK* gene fusion partner, testing methodology, country/region, and prior therapy [type and/or number of lines of therapy])	• Patient demographic and baseline characteristics • Disease history (including pathology report at baseline and subsequently as applicable) • Comorbidities • Method for detecting *NTRK* gene fusion (including testing report at baseline and subsequently as applicable) • ECOG, Lansky, or Karnofsky performance status • Tumor assessments (ORR, DCR, DOR, TTR, PFS, OS) per investigator assessment • Date of radiologic or clinical progression on larotrectinib
• Larotrectinib treatment patterns	• Larotrectinib use (initiation and termination dates, dosage, and dose modification)
• Long-term effects of larotrectinib on growth, developmental milestones, and sexual development in the pediatric cohort • Long-term effects of larotrectinib on neurologic outcomes in all patients	• Developmental milestones; age at adrenarche or menarche (if applicable); Tanner scale • Neurological examination
	• Laboratory examination data; and date of death/last follow-up
**Exploratory:** • Effectiveness of larotrectinib	• Tumor assessments (ORR, DCR, DOR, TTR, PFS, OS) based on radiologic assessments of tumor response per IRC, as applicable

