Larotrectinib was granted accelerated approval based on data from three phase I/II single-arm studies, but safety data are relatively limited, particularly with respect to patient numbers and long-term exposure. ON-TRK is the first prospective, non-interventional study of a TRK inhibitor designed to support the conversion of an accelerated approval to a full approval. The study will provide further evidence to support the safety and effectiveness of larotrectinib in patients with locally advanced or metastatic TRK fusion cancer in real-world practice conditions. Larotrectinib was granted accelerated approval contingent upon fulfilling post-approval requirements in order to obtain full approval. One such requirement is to evaluate an adequate number of patients to characterize response and durability of response for each of the following tumor types: CNS tumors, colorectal cancer, melanoma, and non-small cell lung cancer (NSCLC). A minimum of 40 patients with cancers other than CNS tumors, colorectal cancer, infantile fibrosarcoma, melanoma, NSCLC, salivary cancers, soft tissue sarcoma, and thyroid cancer (e.g., biliary tract cancers, breast cancer, cholangiocarcinoma, gastrointestinal stromal tumors) will also be studied. Evaluating response in these tumor types will further support the tumor-agnostic designation of larotrectinib and may enable additional subgroup analysis by primary tumor type. Another requirement is to conduct a study of larotrectinib following an adequate number of pediatric patients with TRK fusion cancer for 5 years to evaluate the risk of potential long-term adverse effects of larotrectinib on their growth and development; this is covered as a secondary objective of ON-TRK. Patients will be evaluated for age-appropriate growth and developmental milestones and undergo neurological examination at suitable intervals (such as every 6 months) until larotrectinib is discontinued or for at least 5 years, whichever occurs first. In describing AEs requiring dose modifications, ON-TRK will also fulfill another requirement, which is to assess any unexpected risks of SAEs in patients requiring a third dose modification of larotrectinib due to toxicity. An adequate number of adult or pediatric patients with a body surface area of at least 1.0 m^2^ requiring a third dosage modification due to a treatment-related AE will receive larotrectinib 100 mg orally once daily to better describe the tolerability of this approved dosage modification for larotrectinib. The following information will be collected from each patient: age and body surface area (if pediatric), treatment-related AEs leading to the first and second dose reductions of larotrectinib, duration of treatment on prior dose levels, duration of treatment at the 100-mg oral once-daily regimen, best overall response and DOR, and tumor information collected while receiving the 100-mg oral once-daily regimen. An additional request from the FDA was to assess effectiveness by an IRC in this non-interventional study.

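### Pediatric growth is summarized as change in height and weight with no age- and sex-specific reference, so the summary mainly reflects the age mix and cannot by itself show impaired growth or excess weight gain

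*Protocol article*

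**What the plan says.** The growth analysis is one sentence in the Protocol article, Analysis of secondary variables, which applies to the pediatric cohort alone: "change in height and weight from baseline will be summarized at each visit". The cohort is defined under Study design, Participants: "All pediatric patients, regardless of tumor type, will be enrolled within a ‘pediatric’ cohort". Pediatric means under 18, so the cohort can run from infants to 17-year-olds.

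The general rule for continuous variables (Statistical analyses) is absolute values and change from baseline per analysis time point. The same section allows summaries by subgroups such as age and sex where reasonable. No z-score, percentile, height velocity or growth reference is named for height or weight anywhere in the article. The paragraph that holds the growth sentence does plan counts of abnormal findings for Tanner stage, neurological assessment and developmental milestones, but none for height or weight.

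Table 2 lists as a secondary objective: "Long-term effects of larotrectinib on growth, developmental milestones, and sexual development in the pediatric cohort". The variables beside it are milestones, adrenarche or menarche, and Tanner scale, so the sentence on height and weight is the only stated analysis of physical growth. The Discussion gives the regulatory reason: children are to be followed "for 5 years to evaluate the risk of potential long-term adverse effects of larotrectinib on their growth and development".

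**The concern.** Most children get taller and heavier whether or not a drug slows or speeds their growth. A change in centimetres or kilograms says something about a drug effect only when set against what a child of that age and sex would be expected to gain. A control group could supply that expectation, but this study has none. An external growth reference could supply it, but none is stated. What remains is an average (or median) over children whose expected gains differ widely, and its value depends mainly on how many young children contribute at the visit.

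At stake is a question that the study was asked to answer. Growth is a secondary objective and part of a post-approval requirement. A positive mean change at every visit could be read as reassuring although many children were falling away from their expected curve. Weight has the mirror-image problem. In the 55-patient primary dataset described in the Background, weight increase was among the most common grade 3–4 adverse events (7%), and a rise in mean weight in growing children cannot be told from normal growth.

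**Working it through.** **The article's own figures.** The article gives no numerical target for growth. Its only design calculation is the chance of seeing at least one event at 1% incidence in 300 patients. This reproduces, 1 − 0.99^300 = 0.951 against the stated 95%, and has no bearing on the present point.

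**Is a wide age mix plausible?** The Background reports that 52 of 159 patients in the earlier integrated dataset were under 18. Infantile fibrosarcoma made up 56% of these 52. The rest were mainly other soft tissue sarcoma (37%), with a few thyroid cancers, melanomas and congenital mesoblastic nephromas. Infants would be expected to be a large group, next to older children. The mix may also change with time, because the Discussion has growth evaluation run until treatment stops or for at least five years, depending on which comes sooner.

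**Illustration. Every input below is an assumption; none comes from the article.**

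Assumed normal 12-month height gain *g*: infants 22.5 cm (range 20–25), mid-childhood 6 cm (5–7), late teens 0.5 cm (0–1). Assumed age mixes *w* (infant/child/teen): 60/30/10, 33/34/33 and 20/40/40.

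Formulas: mean = Σ *w·g*; SD due to age alone = √[Σ *w·(g − mean)²*].

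| Mix | Calculation | Mean change (range), cm | SD from age alone, cm |
|---|---|---|---|
| 60/30/10 | 0.6×22.5 + 0.3×6 + 0.1×0.5 | 15.4 (13.5–17.2) | 8.9 |
| 33/34/33 | 0.33×22.5 + 0.34×6 + 0.33×0.5 | 9.6 (8.3–11.0) | 9.3 |
| 20/40/40 | 0.2×22.5 + 0.4×6 + 0.4×0.5 | 7.1 (6.0–8.2) | 8.1 |

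Every child in this table grows normally. The range is the mean with all three gains at the lower, then the upper, end of their assumed ranges.

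Now let the infant-rich cohort grow below normal:

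- 25% below: 0.75 × 15.35 = 11.5 cm
- 50% below: 0.50 × 15.35 = 7.7 cm

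Both exceed the 7.1 cm of the normally growing older cohort. The same observed value can thus arise from normal growth or from severe impairment.

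**Within one study.** If the children contributing at a visit had the 33/34/33 mix and not the 60/30/10 mix, normal growth would give a mean lower by 15.35 − 9.63 = 5.7 cm. A 25% impairment in the infant-rich mix lowers it by 0.25 × 15.35 = 3.8 cm. Mix alone moves the summary more than the effect does.

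**Would age subgroups repair it?** Only in part. In infants alone, a 10% shortfall gives 0.9 × 22.5 = 20.3 cm, inside the assumed normal range of 20–25 cm. In mid-childhood, a 15% shortfall gives 0.85 × 6 = 5.1 cm, inside 5–7 cm. Without a stated norm, the raw figure for a band still cannot be classed as normal or impaired.

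The same reasoning applies to weight. No figures were worked for it.

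**The case against.** The strongest objection is that this is a condensed article. One sentence on growth need not be the whole analysis, and the choice of reference and the derivation of scores often sit in the full protocol or SAP, which are not at hand. The article also promises appropriate methods, provides medians and quartiles as well as means, allows age and sex subgroups, and in the Discussion speaks of evaluating age-appropriate growth. The study is descriptive and growth is secondary.

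Some of this stands. The full documents may already standardize, and the article does not rule it out. But the article names a summary for height and weight, and beside it plans abnormal-finding counts for other pediatric outcomes. The point therefore concerns a stated method. The subgroups are conditional and bring no norm. Medians depend on the age mix as means do. The Discussion's remark describes patient evaluation and is not carried into the analysis.

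Three stronger readings are tempting and are not supported:

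- *The study cannot detect drug-related weight gain.* Adverse events are tabulated by Preferred Term, worst CTCAE grade and drug-relatedness, with exposure-adjusted rates, so marked weight gain may appear there. In the expanded safety set (n = 260), moreover, weight increase is not among the most common grade 3–4 larotrectinib-related events listed. The limit concerns the growth summary only.
- *Reporting by visit mixes different times since treatment start.* The article does say that "Examinations and the laboratory monitoring schedule will follow local label recommendations in line with local standard of care", but this does not define how analysis time points are built. Statistical analyses refers to analysis time points, and the Discussion gives six months as an example interval.
- *The shortfall can be stated in centimetres.* The article gives neither growth rates nor an age distribution, so the figures above show direction and plausible scale only.

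**Conclusion.** The point holds for the growth summary as written. Change in height and weight from baseline, over one cohort of all patients under 18, without a control group or an age- and sex-specific reference, cannot by itself show impaired growth or excess weight gain. It does not serve the secondary objective or the requirement "to evaluate the risk of potential long-term adverse effects of larotrectinib on their growth and development". The conclusion rests on two features of the article, the lack of a comparator and the lack of a named reference, and on the general fact that normal growth varies greatly with age. It does not depend on the illustrative numbers. A larger cohort would not help, because the difficulty is one of interpretation and not of precision.

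The weight of the point is moderate. The primary safety analysis and the sample size are untouched. Standardized scores can be derived later from the same measurements, provided that age at measurement and sex are recorded with height and weight. The reason to settle it now is that a reference and a threshold chosen after the data are seen carry less conviction.

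**What to change.** Add to the growth sentence in Analysis of secondary variables:

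1. Height, weight and BMI (derived from the two) will be converted to age- and sex-standardized z-scores against a named growth reference.
2. Change in z-score from baseline will be summarized at the analysis time points, for example every six months to month 60, with the number of children contributing at each.
3. The number and percentage of children whose z-score falls or rises by a pre-set amount will be reported, in line with the counts of abnormal findings already planned for Tanner stage, neurological assessment and milestones.
4. Raw change in height and weight will be kept as supportive information.

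If the full protocol or SAP already does this, a sentence pointing to it is enough. The cost is choosing a reference and a threshold, and programming. Height and weight are already to be analysed and demographics are collected. The sample size does not change.

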#### Analysis of exploratory variables

Effectiveness variables, including ORR, DCR, DOR, TTR, and PFS, will also be determined by an IRC, based on radiological assessments of tumor response as applicable. These effectiveness variables will be determined by an IRC for patients who have technically adequate baseline and on-treatment radiological assessments of tumor response that have been centrally collected at the imaging core laboratory. In patients who had systemic anti-cancer therapy prior to the study, the treatment data will be summarized descriptively. Dosing of other treatment used prior to the study, including start/stop date, duration of treatment, given doses, reasons for discontinuation, and time from discontinuation of treatment to start of larotrectinib, will be retrospectively collected and summarized descriptively in the total study population. For patients with infantile fibrosarcoma, the number and percentage of patients who avoided amputation will be reported. The number and percentage of patients who underwent a surgery for a curative intent while being treated with larotrectinib (excluding amputation) will also be presented. In addition, local protocol amendments may be requested. For example, patient-reported outcomes data will be collected in Austria, Germany, and Canada.

#### Timelines and milestones

The recruitment period will be 36 months. The end of the study for all cohorts, except the pediatric cohort, will happen after the final patient has been in the study for at least 24 months or is no longer under observation, owing to being lost to follow-up, withdrawal, or death. For the pediatric cohort, each patient will be followed up for at least 60 months from larotrectinib initiation unless the patient is discontinued due to loss to follow-up, withdrawal, or death.

The study will be closed 60 months after the last pediatric patient has started treatment with larotrectinib or when no patient is still under observation due to loss to follow-up, withdrawal, or death. For all patients still under observation at time of study closure, a last disease status documentation will be required along with the completion of the final information collection.

Safety reviews will be performed annually, with the first review starting 1 year after the first patient is enrolled. Interim reviews for safety and effectiveness will be performed after approximately 50 patients pooled across tumor types complete at least 6 months of treatment or discontinue treatment. Subsequent reviews will be performed after approximately 150 and 300 patients have met the same conditions. In addition, reviews by cohort type will be performed after approximately 10 patients per cohort complete at least 6 months of treatment or discontinue treatment. The various reviews may be combined if they are expected to occur within approximately 1 month of each other.

